## Abstract

**Background:**

As a common disorder of the gastrointestinal tract, irritable bowel syndrome (IBS) can have negative effects on patients and society, with irritable bowel syndrome with constipation(IBS-C) accounting for a large proportion of these effects. The main clinical manifestations of IBS-C are constipation, abdominal pain, and abdominal distension, which seriously impact the quality of life of patients. The mechanisms of IBS are complex, and the gut-brain axis has been an emerging and recognized theoretical system in recent years. Based on the theory of the gut-brain axis and the theory of Chinese medicine, we designed this study to evaluate the efficacy of one-finger meditation massage in treating IBS-C.

**Methods/design:**

This is a randomized controlled trial. Eligible patients with irritable bowel syndrome (IBS-C) wererandomized 1:1 to a test group (massage plus probiotics) and a control group (probiotics). Patients in the test group weretreated once every 10 days for three consecutive courses of treatment (i.e., three months) and weregiven Bifidobacterium trifolium capsules 630 mg/dose three times daily 30 min after meals every day during the treatment period, with follow-up observations at the end of the third and sixth months of the treatment period. The control group weregiven Bifidobacterium trifolium capsules 630 mg/dose, 3 times a day for 3 months, with follow-up observations at the end of the third and sixth months of the treatment period. The primary outcome indicators are the concentrations of 5-HT and substance P and the IBS Severity Scale (IBS-SSS) assessment. Secondary outcomes are the Bristol Rating Scale (BRSA) score, the IBS Quality of Life Questionnaire (IBS-QOL scale) score, and the assessment of the effectiveness of the evidence. The results wereassessed at the pretreatment, posttreatment, and follow-up stages. Any side effects weresubject to assessment.

**Discussion:**

The aim of this trial is to provide a new method of treatment based on pharmacological treatment that is easy to use, easy to promote and has proven efficacy and to establish the efficacy and safety of treating IBS-C through this trial.

**Registration for Trial:**

Chinese Clinical Trial Registry ChiCTR2200066417 on 5 December 2022. https://www.chictr.org.cn/bin/project/edit?pid=183461

## Background

Irritable bowel syndrome (IBS) is a condition characterized by chronic recurrent abdominal pain, and functional bowel disorders with abnormal bowel movements or changes in bowel habits are some of the most common gastrointestinal disorders [1]. According to the definition, IBS lacks morphological changes and biochemical abnormalities that could explain the symptoms. It is currently a symptom-based diagnosis [2]. Over the past decade, with improved living standards, changing diets and lifestyles, and environmental changes, the number of consultations for this disease has been increasing every year. According to reported statistics, the prevalence of IBS from country to country worldwide is approximately 9–22% in Western countries, and epidemiological studies in Beijing and Guangzhou in China have found that 5.6% of the general population has IBS [3, 4]. In approximately two-thirds of people, IBS is related to their diet; most of them changed their diet, and these modifications caused them to have insufficient food [5, 6], which may be relevant to their gastrointestinal discomfort [6, 7]. Compared with healthy subjects, patients with IBS feel high levels of mental stress. Many patients are depressed, have sleep disturbances, and feel exhausted due to recurrent pain in the abdomen and changes in bowel habits, which lead to fears of serious illness. The overall rate of IBS with psychosomatic disorders is 40–90% [8]. In turn, symptoms of IBS are often exaggerated by stress and/or anxiety [9].

IBS-C is an IBS disease whose etiology and pathogenesis remain elusive. It is generally believed that gastrointestinal motility disorders [10, 11], visceral hypersensitivity [12], abnormal brain-gut axis regulation [13], inflammation of the mucous membranes [14], genetic predisposition to disease [15, 16], nutrition [17] and psychosocial stress [18] are closely related to the development of the disease process. Over the last few years, there has been increasing evidence that the symptoms of irritable bowel syndrome are linked to the regulation of the gut-brain axis [19–21]. A central player in the perpetuation of IBS symptoms is the integrated action and communication between the microbiota and the autonomic nervous system. This signaling pathway is recognized as the gut-brain axis (GBA). The GBA is a bidirectional axis of regulation, consisting of a neuroendocrine network that connects the nervous system between the gastrointestinal tract and the brain and acts as a mutual regulator. The microbiota has a crucial role in this communication [19, 22, 23]. Evidence suggests that immune responses from ecological dysbiosis of the microbiota can contribute to the gastrointestinal symptoms of IBS, which suggests that IBS is actually a disease of both the microbiota and GBA [19]. Brain-gut interactions occur through the neuro-endocrine network system and intestinal flora for gastrointestinal tract-brain interactions [24]. Neuroendocrine cells of the brain-intestinal axis are regulated by the enteric nervous system, autonomic nervous system, and central nervous system and maintain the normal operation of the brain-intestinal axis by secreting related neurotransmitters and hormones [25]. Long-term stimulation by various factors in the internal and external environment can lead to dysfunction of neuroendocrine immune regulation, causing a state of visceral sensory hypersensitivity and malfunction of gastrointestinal tract motility; as a result, abdominal discomfort, changes in bowel habits, pain, fullness, belching, nausea and other abnormalities of the brain and intestinal interaction can occur [26]. The whole process requires the participation of brain-gut peptides, which mainly regulate the gastrointestinal tract by transmitting information between the gastrointestinal nervous system, the central nervous system, and the effector cells of the gastrointestinal tract, thus completing the brain-gut interaction [27]. The main peptides are vasoactive peptide (VIP), neuropeptide Y (NPY), substance P (SP), neuro hypocretin (NT), calcitonin gene-related peptide (CGRP), and 5-hydroxytryptamine (5-HT). The pathophysiological mechanism of constipated IBS is currently considered to be visceral hypersensitivity. Among them, 5-hydroxytryptamine (5-HT) plays an important role in the increased visceral sensitivity of IBS [28]. 5-HT is stored in intestinal endocrine cells, which act on the nerves of the mucous membrane within the lamina propria, activating secretory motor responses and signaling intestinal conditions to the central nervous system by means of visceral afferents; its importance in the control of gastrointestinal function has been confirmed in both animal and clinical studies [29–32].

Irritable bowel syndrome is now classified according to the different clinical stool manifestations: constipation (IBS-C), diarrhea (IBS-D), mixed (IBS-M) or undefined (IBS-U) [33]. IBS-C is characterized by at least 25% of bowel movements of Bristol 1–2 (hard or lumpy stools) and less than 25% of defecating of Bristol 6–7 (loose or watery stools), with fewer than 3 defecations per week [34, 35]. Patients are usually type 1 or type 2 on the Bristol stool scale, with discomfort such as incomplete bowel movements, infrequent bowel movements, abdominal pain, and bloating. Statistically, approximately 35.6% of people with irritable bowel syndrome have a diagnosis of IBS-C, affecting 4.3-5.2% of American adults [36–38]. As a chronic disease, it is not life-threatening, but because of its prolonged symptoms, it has a serious impact on the quality of life of the patient, causes a decline in social functioning, increases the consumption of medical resources, and places a significant economic strain on the patient and society as a whole. Acting in accordance with the report, compared with healthy subjects, subjects with IBS symptoms have lower QOL [39, 40]. Furthermore, there have been reports that people with IBS-C often have reduced productivity due to experiencing distress and dysfunction [41, 42]. Statistically, in the US alone, IBS-C treatment estimates range from $1.3-1 billion per year, with annual indirect costs, mainly due to absenteeism and reduced productivity, ranging from $205 million to $20 billion [43]. Therefore, effective control of IBS-C is a health care issue of critical importance worldwide. However, current treatments for IBS-C currently target only a single symptom, and past studies have shown that treatments that focus only on bowel frequency, such as probiotics used to treat IBS-C that only enhance the frequency of bowel movements, have been relatively unsuccessful, with more than half of IBS-C patients reporting continued constipation [44, 45]. We therefore explored whether a therapy combined with pharmacotherapy could better treat IBS-C, not only by enhancing bowel motility but also by relieving other symptoms, such as abdominal pain and flatulence (bloating), and improving the quality of life and survival of patients, thus achieving greater social and economic benefits.

Massage therapy is one of the oldest forms of healing and has been in use for centuries in many civilizations and cultures, including China [46]. Massage therapy promotes blood and lymphatic fluid circulation, relieves muscles, removes the dross, and encourages body and mind relaxation [47, 48]. By stimulating the abdominal muscles and increasing abdominal pressure, abdominal massage promotes peristalsis of the gastrointestinal tract [49]. Abdominal massage has been reported to improve constipation by mechanically stimulating the associated neurologic/autonomic response [50–53]. Abdominal massage increases local and visceral circulation and decreases the time it takes for stool to pass by stimulating colonic motility [51–54]. One-finger meditation massage is a traditional Chinese medical massage therapy that stimulates the point lightly and is now widely used clinically for various diseases. One-finger meditation massage therapy has been used for over 200 years and is guided by the basic theories of Chinese medicine, such as the theory of yin and yang, five elements, meridians, and internal organs. The one-finger meditation pushing method has the unique advantages of a small contact area, powerful but not losing softness, deep penetration, and concentration. It has been reported that abdominal massage can treat insomnia, functional constipation, chronic gastritis, abdominal distension, and other diseases. In this paper, we describe a randomized controlled study on the IBS-C system and comprehensively and objectively observed and analyzed the clinical efficacy of one-finger meditation massage pushing abdominal acupuncture points in the treatment of IBS-C. Traditional Chinese medicine has a history of thousands of years, including Chinese massage. It has a unique theoretical system and traditional therapies have been shown to be effective in clinical trials and basic animal studies. Now we are trying to interpret our theories in a modern scientific way, and tens of thousands of clinical researchers have used modern medical theories to confirm the efficacy and safety of traditional therapies. In this study, we are trying to combine the theoretical system of the gut-brain axis with one-finger meditation massage for the first time. We are attempting to demonstrate that stimulation of acupuncture points using the one-finger meditation massage can regulate 5-HT and P substances and validate the theoretical system of the gut-brain axi. This approach has many advantages, such as being painless, economical, fast-acting, and providing significant long-term effects.

## Methods

### Objective

The overall objective of the study is the evaluation of the clinical rationality of the one-finger meditation massage of the abdomen for treating patients with irritable bowel syndrome (IBS-C), providing a basis for clinical promotion, to have better long-term efficacy compared with drug treatment alone, to take advantage of its painlessness and higher patient compliance, and to provide an exact and effective treatment for IBS-C in Chinese medicine.

### Trial design

This trial is a single-center randomized, blinded trial in which outcome assessors were blinded to compare the efficacy of one-finger meditation massage combined with probiotic therapy versus pharmacotherapy in patients with IBS-C, which were conducted at Zhejiang Hospital. In total, 66 participants with IBS-C were randomly assigned to the trial and control groups. The protocol was registered on the following website: www.chictr.org.cn (No. ChiCTR2200066417). Protocol reporting is fully compliant with the SPIRIT guidelines [55]. Figure 1 shows the flowchart of the study process. In addition, the schedule for enrolling, treating and evaluating the trial is shown in Fig. 2.

**Fig. 1 Fig1:**
[figure not shown]
Flow chart of the study process. 5-HT, 5-hydroxytryptamine, SP, substance P, IBS-SSS, IBS Severity Scale, BRSA,Bristol Rating Scale Assessment, IBS-QOL, IBS Quality of Life Questionnaire

**Fig. 2 Fig2:**
[figure not shown]
Schedule of enrolment, treatments, and assessments. O, required; 5-HT, 5-hydroxytryptamine; SP, Substance P; IBS-SSS, IBS Severity Scale (IBS-SSS) assessment; BRSA, Bristol Rating Scale Assessment; IBS-QOL, IBS Quality of Life Questionnaire

### Participants, recruitment, and ethics

Recruitment of participants were from Zhejiang Hospital in two ways: recruitment posters and online recruitment. Participants were informed of the inclusion and exclusion criteria, interventions, intervention times, and other positive trial considerations during recruitment. Participants who meet the recruitment criteria will again be provided with the above information. After obtaining patient consent, patients will sign an informed consent form and be randomly assigned to a group. The Zhejiang Hospital Ethics Committee approved the study protocol (No. 2021 Pro-Audit No. 15 K).

### Diagnostic criteria

Refer to the < Rome IV Diagnostic Criteria for Functional Gastrointestinal Disorders>.

IBS typically presents with recurrent episodes of abdominal pain, at least 1 day per week for the last 3 months, associated with 2 or more of the following: (1) bowel movements; (2) changes in bowel frequency; and (3) changes in stool characteristics (appearance). IBS Constipation (IBS-C): At least 25% of bowel movements are Bristol 1–2, and less than 25% of bowel movements are Bristol 6–7.

### Inclusion criteria

Subjects with all of the following conditions were included: (1) meet the Western medicine diagnostic criteria of IBS-C; (2) aged between 20 and 80 years; (3) can adhere to the treatment as planned and can receive follow-up; (4) patients are conscious and can actively cooperate with the treatment, examination and complete the correct description of the assessment items; and (5) patients themselves or their relatives sign the informed consent.

### Exclusion criteria

Subjects with one of the following conditions were excluded: (1) those not meeting the above diagnostic and inclusion criteria; (2) pregnant or lactating patients; (3) patients with serious life-threatening primary diseases, including cardiovascular, cerebrovascular, hepatic, renal, hematopoietic and psychiatric diseases; and (4) those who receive other relevant treatments that may affect the observation of effect indicators in this study.

### Randomization and allocation concealment

An independent statistician who is not involved in the study will generate the randomization group: the numbers were randomly divided into two Groups A and B at a ratio of 1:1, i.e., A (Test group: Massage with the probiotic group) and B (Control group: probiotic group), using SPSS 19.0 software before the formal trial. The random sequence of the generated numbers and the grouping information were kept by the person in charge and kept confidential. Opaque brown envelopes were made according to the number of included cases, and the envelopes were numbered sequentially according to the order of numbers on the surface of the envelopes. The envelopes will contain the grouping information corresponding to the random sequence of numbers on the surface of the envelopes, such as 1(A) and 2(B). After signing the informed consent form and completing the basic information form, the envelopes were opened strictly in the order of the numbers on the envelopes, and patients were allocated to groups (trial or control) in accordance with the protocol in the envelopes.

### Blinding

This is a participant-rater-blinded study, meaning that participants do not know the group to which they belong. Participants have a 50% chance of being assigned to the test and control groups: massage with the probiotic group and probiotic group. The patient’s group allocation is also unknown to the follow-up assessors. Although the massage therapist will not be blinded to his or her treatment assignments, the massage therapist will not be part of the outcome assessment or data analysis.

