### Intervention

#### Test group (massage with probiotic group)

The acupuncture points and areas are as follows: Zhongwan (RN12), Tianshu (ST25), Guanyuan (RN4), Qi Hai (RN6), Pishu (BL20), Shenshu (BL23), Dachangshu (BL25), Mingmen (DU4), Zusanli (ST36), Zhi Gou (SJ36) and abdomen. The locations of all selected acupoints are shown in Table 1. Operations: (1) Using the one-finger meditation massage method, the patient is in a supine position, and the operator uses the one-finger meditation massage method to push ST25, RN4, RN6, and RN12 for 2 min each; the one-finger meditation massage method requires concentration, sinking shoulder, dropping elbow, hanging wrist, palm deficiency, finger solid, tight pushing, and slow moving. The frequency of swinging is approximately 120–160 times/min; (2) Two minutes of clockwise abdominal massage; (3) Press and knead SJ36 and ST36 points for 1 min each; (4) The patient is in a prone position and rubs the lumbar back, BL23, DU4, BL20, and BL25 for approximately 2 min to penetrate the heat. The manipulation should be even, gentle, persistent, and powerful to achieve deep penetration; (5) Course of treatment: 10 days once, 3 times as a course of treatment, three consecutive courses of treatment (i.e., three months). The patient were given Bifidobacterium trifolium capsules (Shanghai Xinyi Pharmaceutical Co., Ltd., State Drug Administration S0950032) 630 mg/d, 3 times/d, 30 min after the meal for three months.

**Table 1 Tab1:** Location of acupoints for treating IBS-C

Acupoints	Location
Zhongwan(RN12)	On the anterior median line, midpoint of the line connecting the lower end of the sternum and the belly button
Mingmen(DU4)	Interspinous process of the second and third lumbar vertebrae
Guanyuan(RN4)	In the lower abdomen, on the anterior median line, when the umbilicus is 3 cun below the middle.
QiHai(RN6)	In the lower abdomen. On the front median line, 1.5 cun below the middle of the umbilicus
Pishu(BL20, bilateral)	Under the spinous process of the 11th thoracic vertebra, open 1.5 cun laterally
Shenshu(BL23, bilateral)	Under the spinous process of the 2th lumbar vertebra, open 1.5 cun laterally
Dachangshu(BL25, bilateral)	Under the spinous process of the 4th lumbar vertebra, open 1.5 cun laterally
Tianshu(ST, bilateral)	In the abdomen, at the same level as the navel, 2 cun away from the front median line.

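### Participants cannot be blinded to massage versus no massage, so the participant-blinding claim should be withdrawn and the symptom outcomes read accordingly

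*Protocol article*

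**What the plan says.** The Blinding section claims blinding of participants as well as raters: "This is a participant-rater-blinded study, meaning that participants do not know the group to which they belong". It names the two arms as "massage with the probiotic group and probiotic group", adds that follow-up assessors do not know the allocation, and says that the massage therapist is unblinded but takes no part in assessment or analysis.

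Trial design describes a "single-center randomized, blinded trial in which outcome assessors were blinded" and mentions no other blinded party.

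The test-arm section describes manual treatment: "the patient is in a supine position, and the operator uses the one-finger meditation massage method". The schedule is "10 days once, 3 times as a course of treatment, three consecutive courses of treatment (i.e., three months". The control-arm section lists the same capsules plus advice on habits and diet. It lists no massage, sham or attention control.

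On what participants know beforehand, Participants, recruitment, and ethics says: "Participants were informed of the inclusion and exclusion criteria, interventions, intervention times, and other positive trial considerations during recruitment". It continues: "Participants who meet the recruitment criteria will again be provided with the above information".

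The primary outcomes are serum 5-HT, serum SP and IBS-SSS. IBS-QOL, the Bristol scale and a graded efficacy evaluation are secondary.

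**The concern.** Blinding of participants is stated as a fact about the trial, yet the arms differ by a procedure that no recipient could miss. If the statement is carried into the trial report, readers will take the symptom results as protected from expectation and attention effects when they are not.

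This matters most for IBS-SSS, which is a primary outcome, and for IBS-QOL. Both ask about symptoms and their effect on daily life. A between-arm difference on them could come from the massage itself, from nine extra sessions of personal contact, from knowing that one is receiving the studied treatment, or from any mixture of these. Believing participants to be blinded would wrongly exclude the last explanation.

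**Working it through.** **1. Can a participant tell the arms apart?**

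| Element | Test arm | Control arm | Source |
|---|---|---|---|
| Capsules | yes | yes | both intervention sections |
| Hands-on massage | 3 per course × 3 courses = 9 sessions | none | Test group; Control group |
| Sham or attention control | not applicable | none described | Control group |
| Lifestyle and diet advice | not listed | listed | Test group; Control group |
| Told the interventions and times beforehand | yes | yes | Participants, recruitment, and ethics |

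The groups are defined by massage or no massage, and participants have been told what the interventions are. Receiving or not receiving the first session therefore reveals the group. The claim in Blinding is incompatible with the two intervention sections and with the recruitment section.

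**2. Which outcomes does this reach?**

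- IBS-SSS: pain severity, pain days, bloating, bowel satisfaction and effect on life. The article does not say who completes it. Its items, and the inclusion criterion that patients can describe the assessment items correctly, point to patient rating.
- IBS-QOL: mood, self-image, social functioning and similar dimensions. The same inference applies.
- Efficacy grade: a percentage change in a score, described in terms of main symptoms and signs. The article does not say which score, so exposure is probable rather than certain.
- Serum 5-HT and SP: measured by ELISA, so much less open to reporting bias.

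A blinded assessor who records an unblinded patient's rating does not make that rating blind.

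**3. Is the sample size affected?**

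The stated figure reproduces. With 0.90 versus 0.60, two-sided α = 0.05 and power 0.80, the arcsine formula n = 2[(1.96 + 0.84)/h]², where h = 2·arcsin√0.90 − 2·arcsin√0.60 = 0.726, gives 29.8, so 30 per arm and 60 in total. Then 60 × 1.10 = 66, as stated. The number of patients is not at issue. If the 90 and 60 are efficacy-grade rates, which the article does not say, the comparison used for sizing is also exposed.

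**4. How large could the effect be?**

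No document figure gives the bias, so this is an illustration on assumed values. Suppose massage has no true effect and knowledge of allocation shifts a self-reported score by δ SD. A two-sample t-test with n = 30 per arm has 58 degrees of freedom, critical value 2.002 and noncentrality δ√(n/2) = 3.873δ.

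| Assumed δ | Noncentrality | Probability of p < 0.05 |
|---|---|---|
| 0 | 0 | 5.0% |
| 0.2 | 0.775 | 11.9% |
| 0.3 | 1.162 | 20.8% |
| 0.5 | 1.936 | 47.8% |

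With 33 per arm the last three become 12.6%, 22.5% and 51.6%. The contradiction in step 1 does not depend on these figures.

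**The case against.** Several objections limit the scope of the point.

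- *A condensed article may omit a sham.* This does not rescue the claim. Both arms are described in operational detail, and the control is called simply the probiotic group throughout. The fault is a positive statement, not an omission.
- *The stated objective is an add-on comparison with drug treatment alone.* This stands. Such a question can be answered without a sham, so a reader should not infer that the design is invalid or that a sham arm is required. Moreover, the point-stimulation aim in Background is tied to 5-HT and SP, not to symptoms.
- *Two of the three primaries are laboratory assays.* This also stands. A reader might infer that the trial's primary result as a whole is open to reporting bias; the documents support that only for IBS-SSS.
- *Trial design does not contradict Blinding.* Correct. A reader might take "randomized, blinded trial in which outcome assessors were blinded" to mean assessors only, but the section does not say so. It is less complete than Blinding, not opposed to it. The contradiction lies between Blinding and the intervention and recruitment sections.
- *Assessor blinding may hold.* Nothing in the article shows otherwise, and this point does not dispute it.
- *The size is unknown.* True. The table shows what an assumed bias would do, not what happens in this trial.

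**Conclusion.** The statement that participants do not know their group is wrong as written and must be corrected. It conflicts with the described content of the two arms and with what participants are told before consent. IBS-SSS and IBS-QOL, and probably the efficacy grade, are open to expectation and attention effects; serum 5-HT and SP are less so.

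The conclusion on blinding rests on the text alone. The consequence for outcomes rests on one inference, that the symptom scales are patient-rated, which their items make very likely. The size of any bias cannot be derived from the documents, and the rejection rates of 12% to 48% for 0.2 to 0.5 SD are assumptions for illustration only.

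A related limit is that the arms as written differ by more than massage, because lifestyle advice appears only under the control arm. Until that is settled, even the add-on contrast is not cleanly defined.

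**What to change.** - In Blinding, delete the participant-blinding claim. There and in Trial design, describe the trial as assessor-blinded only, with participants and massage therapist unblinded.
- Do not claim that the ELISA laboratory or the analysing statistician is blinded unless this is actually put in place; the article does not say that either is.
- Instruct patients not to disclose their arm to the follow-up assessors, including in telephone follow-up. This protects the assessor's blinding but does not remove the patient's own expectation.
- State the performance and reporting bias for IBS-SSS and IBS-QOL as a limitation.
- Limit the conclusion on symptoms to the effect of adding massage sessions, including contact and expectation, to probiotics. Do not attribute it to point stimulation itself.
- Reconcile the two intervention sections on whether the lifestyle advice is given to both arms, and word the comparison to match.

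**Cost:** mostly wording, plus one small procedural instruction, which can help only at visits still to come. No new arm or patients are needed. The price is a less favourable blinding statement and a narrower causal claim.
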